## Introduction

Physical activity is important for healthy ageing. Some of the benefits of regular physical activity for older people include reduction in falls,^1^ better physical functioning^2^ and improvement in well-being.^3^ The recommended physical activity level for older adults aged 65 years and above is to achieve 150 min of moderate physical activity in a week, with 2 days of strength training.^4^ This is often expressed as 30 min of brisk walking or equivalent activity 5 days a week, although 75 min of vigorous intensity activity spread across the week, or a combination of moderate and vigorous activity are also suggested.^5^

Despite strong evidence for the benefits of physical activity, physical inactivity remains a significant problem among older adults worldwide.^6^ Studies in the UK have shown that less than 7% of community-dwelling older adults achieve the recommended weekly physical activity level.^7 8^ The COVID-19 pandemic has exacerbated the problem of physical inactivity.^9^ Rules on social distancing and shielding of vulnerable groups have resulted in increased physical inactivity among older people, with potentially widespread deconditioning.

The rise of the use of technology during the pandemic may provide a solution to address the problem of physical inactivity among older people. Older adults are embracing modern technology more than ever before and are increasingly familiar with the use of devices and online platforms to stay in touch with their family members and friends.^10 11^ This presents the opportunity to develop online physical activity interventions for older adults to promote increased physical activity. A review of reviews conducted by McGarrigle and Todd found low to moderate evidence that physical activity interventions delivered through the internet and related technologies may be effective in increasing physical activity among older adults in the short term.^12^ Online group exercises have been shown to be feasible for older adults.^13^ However, there is little evidence on the use of trained volunteers to lead such exercise groups.

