## Methods and analysis

### Study design

A quasi-experimental mixed-methods approach will be used to determine the feasibility and acceptability of implementing online volunteer-led exercise sessions in community clubs. The study will be conducted at community-clubs focused on promoting social interaction among older people. Feasibility studies are used to determine whether an intervention is appropriate for further evaluation, to determine sample sizes for controlled trials and to assess whether the ideas and findings can be shaped to be relevant and sustainable. In this study, the feasibility of training volunteers to promote increased physical activity among community-dwelling older adults will be assessed. The acceptability of the intervention will be examined through qualitative interviews to explore the views and experiences of volunteers, older adults participating in the study, and their carers or family members. The impact of the intervention on physical activity levels and functional outcomes will also be measured. This will help inform the sample size calculation for a future effectiveness trial.

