#### Exercise participant recruitment

Club members who are interested in participating in the online group exercise will indicate their interest to club staff or approach the research team directly. Participant information sheet and consent forms will be posted to club members.

The inclusion criteria for the group exercise participants are: adults aged 65 years and older, able to walk with or without a walking aid, and able to provide written consent (box 1). Participants who are actively participating in other online exercise classes will be excluded. The aim is to recruit 30 older adults attending social clubs who do not engage in regular exercise.

Box 1Inclusion and exclusion criteriaInclusion criteriaOlder adults aged >65 years.Able to walk, with or without a walking aid.Able to provide written consent.Exclusion criteriaActively participating in other online exercise classes.

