### Data analysis plan

#### Quantitative data analysis

Data collected will be double entered into a secured database for analysis. Statistical analysis will be conducted using the statistical software SPSS Statistics V.25. Descriptive statistics—median (IQR); mean (SD); number (%)—will be used to analyse the numbers of volunteers recruited, trained, and retained, as well as the type and extent of progression of the seated exercise, and duration of their activity, and patients’ adherence to the intervention. Analysis of the above outcome measures will be used to develop an assessment of the feasibility of delivering this intervention. Adherence to the intervention and reasons for non-adherence will be reported.

Outcome measures recorded at baseline will be compared with measurement at 6 months to determine if the PA intervention had an impact on physical activity levels measured by CHAMPS, functional outcomes including performance in ADLs (Barthel Index), quality of life (EQ-5D-5L), frailty status (PRISMA-7) and sarcopenia status (SARC-F). The distribution of each outcome measure will be assessed for normality. Depending on the skew of the data, parametric (t-test) or non-parametric (Mann-Whitney U test) statistics will be used for continuous variables. χ^2^ test will be used for categorical variables.

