#### Strengths and limitations of the study

This study explores a novel approach of training volunteers to deliver online group exercise to older adults. Application of a mixed-methods approach in this study will help determine the feasibility of the intervention and explore barriers and facilitators to a successful implementation of the intervention. However, a limitation of the study is the lack of a control group. Recruitment of older adults will be through established social clubs, in which recruiting some older adults and excluding others from participating in the exercise groups would be a challenge. Additionally, as this is a feasibility study, we will use a range of social clubs of varying sizes, and client groups with different age ranges and physical abilities, to explore different approaches to the intervention rather than including a control group. Nevertheless, this study has been designed to assess the feasibility and acceptability of the intervention with a view to informing the development of a toolkit to support the wider implementation of the intervention and a future controlled experimental design. This study excluded older adults who are not able to walk. Patients who are bed-bound will not be able to participate in the seated exercises without additional support. This additional support cannot be met by this study. As the intervention is delivered remotely, participants must have a level of independence to participate safely. Additionally, one of the key outcome measure is physical activity levels and older adults who are bed-bound will have minimal activity levels.

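### The uncontrolled before-after comparison is planned to determine impact, which one arm cannot show, and the text leaves open that the observed change will size the next trial

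*Protocol article*

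**What the plan says.** All places are in the protocol article.

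- **Quantitative data analysis.** Baseline is to be "compared with measurement at 6 months to determine if the PA intervention had an impact on physical activity levels measured by CHAMPS", and likewise on the Barthel Index, EQ-5D-5L, PRISMA-7 and SARC-F. The methods named are a t-test or Mann-Whitney U test for continuous variables and a chi-square test for categorical ones.
- **Study design.** The design is called quasi-experimental. The section then says: "The impact of the intervention on physical activity levels and functional outcomes will also be measured". The next sentence is: "This will help inform the sample size calculation for a future effectiveness trial". It does not say which quantity will be carried forward.
- **Abstract, Analysis.** This also speaks of the intervention's impact on health outcomes. It assigns that to descriptive statistics and then lists the same tests.
- **Strengths and limitations of the study.** "However, a limitation of the study is the lack of a control group". The section explains why (recruitment runs through established clubs, and the purpose is feasibility) and looks ahead to a controlled design. It does not say that before-after change will not be attributed to the intervention.
- **Exercise participant recruitment.** "The aim is to recruit 30 older adults attending social clubs who do not engage in regular exercise".
- **Introduction.** "Rules on social distancing and shielding of vulnerable groups have resulted in increased physical inactivity among older people".

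**The concern.** Whether an intervention had an impact is a question about what would have happened without it. Two measurements on one group do not answer that, whichever test is used, so an analysis plan that is not shown here could not repair it. The purpose itself is wrong as stated.

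The article gives specific reasons why scores might move without the exercise classes:

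- Restrictions are said to have reduced activity in this population, and they may ease or tighten over six months.
- The study seeks people who are not regular exercisers, so some upward drift on re-measurement is expected.
- CHAMPS is self-reported.
- Each person's two assessments fall half a year apart, so season may contribute.

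Two things are at stake. A change due to time could be published as an effect of volunteer-led exercise. It could also be taken as the effect size for the effectiveness trial, because the sizing sentence directly follows the impact sentence.

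**Working it through.** **What there is to reproduce.** The article gives a target of 30 participants and no alpha, power, effect size, SD, correlation or drop-out for this comparison. There is no stated figure to check. Everything below is illustrative: 30 comes from the recruitment section and every other input is assumed. The article says only t-test; the paired form is my assumption.

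**1. How often a background shift looks like an impact.** Let the intervention effect be zero and let scores drift by g SDs of the individual change. The paired t statistic is then noncentral t with n − 1 degrees of freedom and noncentrality g√n. For n = 30 the two-sided 5% critical value is 2.045. For g = 0.3 the noncentrality is 0.3 × √30 = 1.64.

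| Drift g (SD of change) | P(significant), n = 30 | P(significant), n = 24 (assumed 20% loss) |
|---|---|---|
| 0 | 5% | 5% |
| 0.1 | 8% | 8% |
| 0.2 | 19% | 16% |
| 0.3 | 36% | 29% |
| 0.5 | 75% | 65% |

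**2. Is a drift of that order plausible?** Consider regression to the mean alone. If participants came from the less active half of a normal distribution of baseline scores, their mean would lie 0.798 SD below the population mean. The expected rise is then (1 − r) × 0.798 outcome SDs, where r is the test-retest correlation:

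- r = 0.5: 0.40
- r = 0.7: 0.24
- r = 0.8: 0.16
- r = 0.9: 0.08

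At r = 0.7 the SD of change is about √(2 × 0.3) = 0.77 outcome SDs, so the rise is 0.24 / 0.77 ≈ 0.31 SD of change, close to the 0.3 row above. This is a generous case. Not exercising regularly is stated as a recruitment aim, not as a cut-off on the baseline CHAMPS score, and selection on a stable habit would produce less regression.

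**3. What follows if the observed change is used as the target difference.** Suppose it is read as a standardised between-arm difference of 0.5. With 80% power at two-sided 5% (normal approximation), n per arm = 2(1.960 + 0.842)² / 0.5² = 62.8, so 63. If the true controlled effect is smaller:

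| True effect | Power with 63 per arm | Needed per arm for 80% |
|---|---|---|
| 0.4 | 61% | 99 |
| 0.3 | 39% | 175 |
| 0.2 | 20% | 393 |

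**4. What the study can supply.** An SD needs no control group. From the chi-square interval with 29 degrees of freedom, the 95% limits are 0.80 to 1.34 times the estimate. Required sample size scales with the SD squared, so it could be 0.63 to 1.81 times the planned value. With 24 completers the ranges are 0.78 to 1.40 and 0.60 to 1.97. This is usable but imprecise. The baseline-to-follow-up correlation, retention and adherence can also be estimated from one arm.

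**The case against.** The strongest reply is that this is a feasibility study and says so. Feasibility is the primary outcome, none of the four listed objectives concerns effectiveness, the missing control group is declared and explained, and a controlled design is deferred to later work. The abstract even assigns the health outcomes to descriptive statistics. This stands as a limit on severity. It does not remove the point, because declaring the limitation while keeping an aim that the limitation rules out leaves the two sections in conflict.

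Several stronger readings are tempting, and the article does not support them:

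- **That the design cannot help size a future trial.** It can, through the SD, correlation and retention. The article says only that the work will help inform the calculation.
- **That the observed change will be the target difference.** No parameter is named. The order of the two sentences suggests it and no more.
- **That season biases every club in the same direction.** No start dates are given, and the sessions are piloted in one club before being extended, so starts may be staggered.
- **That the encouragement, booklet and diary are confounders.** They belong to the intervention. A real increase through them is an intervention effect; only distorted reporting is a rival explanation.
- **That five unadjusted tests are a fault in themselves.** A family-wise error of 1 − 0.95⁵ = 23% needs five independent tests at an alpha the article does not state, and these measures overlap in content. Unadjusted secondary outcomes are ordinary in a feasibility study.

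The imprecision of estimates from 30 people is also no proof of this flaw. It is random error, which a small controlled study would share; the problem here is bias.

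**Conclusion.** The point holds for attribution. The tests are given a purpose that a single-arm, two-time-point design cannot serve, and the limitations section does not withdraw it. On sizing it holds only in part: the study can inform the SD, correlation, retention and adherence, but not the treatment effect, and the text is ambiguous about which is meant.

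The size depends on an unknown drift. Across the assumed range of 0.1 to 0.5 SD of change with 30 participants and no intervention effect, a nominal 5% test is significant 8% to 75% of the time, and 36% at 0.3. These figures assume a paired t-test and normal changes. They show sensitivity and do not predict what this study will find.

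This should be corrected, but it does not threaten the study: the outcomes affected are secondary.

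**What to change.** 1. In the abstract's Analysis paragraph, the Study design section and the Quantitative data analysis section, replace the impact wording with within-person change from baseline to 6 months, reported with 95% confidence intervals. Label any tests exploratory.
2. State, in the analysis section as well as the limitations, that change will not be attributed to the intervention because there is no comparator. Name restrictions, regression to the mean, season and self-report as alternative explanations.
3. Say which quantities will inform the future sample size: the SD, baseline-to-follow-up correlation, retention and adherence, with their uncertainty. State that the observed mean change will not be the target difference, which should come from a minimum important difference.

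The cost is a few sentences, with no new data and no change to recruitment or delivery. The real price is that the paper can no longer claim an impact on activity or function. The primary feasibility outcome and the qualitative work are unaffected.

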**Analysis:**

Simple descriptive statistics will be used to describe participant characteristics, the feasibility of the study and the impact of the intervention on health outcomes. Parametric(t-test) or non-parametric(Mann-Whitney U test) statistics will be used to analyse continuous variables. χ^2^ test will be used for categorical variables. Qualitative data will be analysed using an inductive thematic analysis approach.

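### The normality check is aimed at the outcome scores and then picks the test, although the comparison rests on within-person change, and no effect estimate is fixed for any score

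*Protocol article*

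**What the plan says.** Under Quantitative data analysis the protocol article sets out the comparison for the secondary outcomes: "Outcome measures recorded at baseline will be compared with measurement at 6 months". The rule for choosing a method follows: "The distribution of each outcome measure will be assessed for normality", and then "Depending on the skew of the data, parametric (t-test) or non-parametric (Mann-Whitney U test) statistics will be used for continuous variables". The Abstract names the same two tests. Within-person change is not mentioned in either place.

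Three other statements bear on the point:

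- The Strengths and limitations section says that "a limitation of the study is the lack of a control group", so every comparison is before against after in the same people.
- Study design gives a purpose for measuring the impact on activity and function: "This will help inform the sample size calculation for a future effectiveness trial".
- The Abstract promises description whichever test is chosen: "Simple descriptive statistics will be used to describe participant characteristics, the feasibility of the study and the impact of the intervention on health outcomes". The analysis section lists the forms of description, but that sentence concerns feasibility: "Descriptive statistics—median (IQR); mean (SD); number (%)—will be used to analyse the numbers of volunteers recruited, trained, and retained".

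**The concern.** With one group measured twice, the quantity of interest is each person's change. A t-based analysis of such data rests on the distribution of the changes. Skew that a person carries at both times cancels in the difference, so checking the scores answers a different question. The protocol does not literally say raw scores, but it refers to each outcome measure and names Mann-Whitney, which takes two sets of scores, so that is the natural reading. The fault would remain if only the test names were changed to paired versions.

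Skew is plausible here. CHAMPS activity time cannot fall below zero, and recruitment targets people who do not exercise regularly.

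At stake is what gets reported. The rule selects a p-value outcome by outcome, after the data are seen. Planning a later trial needs an SD, and preferably the SD of the change or the correlation between the two times. A rank test by itself supplies none of these.

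**Working it through.** The protocol gives no alpha, power, SD, correlation or dropout, so there is no figure of its own to reproduce. Its only numerical input is the recruitment aim of 30. Everything else below is assumed: two-sided 5% level, Shapiro-Wilk at 5%, and either 30 pairs or 27 completers (3 of 30 lost).

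**Step 1: why skew in the scores need not reach the change.** Write the baseline score as P + E1 and the 6-month score as P + E2 + δ, with person level P, independent normal errors, total variance 1 and correlation ρ = var(P). The change is δ + E2 − E1, from which P has dropped out. If P is exponential (skewness 2), each score has skewness 2ρ^1.5, which is 0.71, 1.17 and 1.43 at ρ = 0.5, 0.7 and 0.8. The change has skewness 0.

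**Step 2: how often each check fails.** The figures come from 4,000 simulated studies per setting. The scores count as failing if either time point fails.

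| Assumed distribution | n | Scores fail | Change fails |
|---|---|---|---|
| Normal throughout | 30 | 9–11% | 4–5% |
| Exponential person level, normal error, ρ = 0.5 / 0.7 / 0.8 | 30 | 35% / 59% / 72% | about 5% |
| Log-normal, log SD 0.4, ρ = 0.7 | 27 | 71% | 22% |
| Log-normal, log SD 0.6, ρ = 0.5 | 27 | 95% | 40% |
| Log-normal, log SD 0.8, ρ = 0.5 to 0.8 | 30 | over 99% | 66–72% |

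A small part of the gap arises because two scores are checked against one change: two independent 5% checks give 1 − 0.95² = 9.75%, in line with the first row. The rest is skew that cancels.

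**Step 3: does the misdirected check damage the test?** Take the rule with its tests made paired: signed-rank if either score fails, otherwise paired t. Compare it with always using paired t (27 pairs, 3,000 runs, shifts giving the paired t-test a power of about 0.6 to 0.7).

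| Assumed distribution | Type I error, rule / always t | Power, rule / always t | Difference in power |
|---|---|---|---|
| Gamma person level, normal change | 4.4% / 4.8% | 0.685 / 0.701 | −0.016 |
| Log-normal, log SD 0.6, ρ = 0.5 | 5.3% / 4.5% | 0.647 / 0.590 | +0.057 |
| Log-normal, log SD 0.4, ρ = 0.7 | 5.3% / 4.9% | 0.629 / 0.617 | +0.012 |

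The Monte Carlo standard error of a 5% rate is √(0.05 × 0.95 / 3000) = 0.4 percentage points, so none of these error rates is clearly off 5%. Power falls by at most 0.016 and in two settings rises.

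**Step 4: what a later trial needs.** With a common SD σ at both times, the SD of the change is σ√(2(1 − ρ)): 1.00σ, 0.775σ and 0.632σ at ρ = 0.5, 0.7 and 0.8. The size of a trial analysed on change scales with the square: 1.00, 0.60 and 0.40. Between ρ = 0.5 and ρ = 0.8 the required number differs by a factor of 1.00 / 0.40 = 2.5. Neither test statistic supplies ρ, and the SDs at the two times do not give it on their own.

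**The case against.** The strongest objection is that the rule selects a hypothesis test and does not limit what is reported. A reader might infer that a skewed outcome loses its mean and SD. The documents do not support that. The Abstract plans descriptive statistics for the impact on health outcomes whichever test is used, nothing says means or SDs are dropped with a rank test, and both can be computed from the pairs. This part of the objection stands in full.

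A reader might also infer that moving to a rank test discards a valid analysis and so harms the inference. Step 3 shows otherwise: one valid paired test is exchanged for another of about equal, sometimes better, power. A switch made on the changes is also harmless, with type I error of 4.3 to 5.5% and power within about 0.02 of the better single test at 30 pairs.

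Third, the wording does not strictly exclude change scores, and a condensed article may leave reporting detail to a fuller plan. That has some force. But the article does fix a rule. It aims the check at the outcome measures, pairs it with a test that operates on scores, and makes the method depend on the data. That is a stated choice, and it sits poorly with the stated purpose of informing a sample size.

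Finally, the larger fault in the same sentence is that Mann-Whitney is an independent-samples test and the t-test is not said to be paired. Under normal data with ρ = 0.7, a shift of 0.4 SD and 30 pairs, the unpaired t-test has power 0.23 against 0.78 for the paired one. That is a separate point. The present one remains after it is corrected, but is much smaller.

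**Conclusion.** The point holds in a limited form. On its natural reading the rule checks the wrong distribution: scores fail in about one third to over 90% of simulated studies with skewed scores, the changes in about 5 to 40%, rising to 66 to 72% under very strong skew. These rates rest wholly on assumed shapes, correlations and 27 to 30 pairs. The widest contrasts need a normal change, which the protocol cannot vouch for.

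The effect on type I error and power is negligible once the tests are paired. What remains concerns estimation: the reported quantity may differ in kind between outcomes, and the plan does not commit to the mean change, its SD or an interval, although the data are to feed a sample size calculation. Since these are secondary outcomes in an uncontrolled feasibility study, the improvement is minor.

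**What to change.** Drop the normality switch as the rule for what is reported. For every score, pre-specify the mean within-person change with a 95% CI, using a bootstrap interval where the changes are skewed. Report the SD at each time, the SD of the change and the baseline-to-6-month correlation, with median and IQR as added description. If a test is also given, use a paired one and judge its assumptions on the changes.

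This replaces two sentences, needs no further data, and is best done together with the correction of the unpaired tests. The downside is that a mean change is a less natural summary for strongly skewed scores, which the medians help to cover, and that a signed-rank test can be somewhat more powerful there.

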These outcome measures will be recorded at baseline, using remote assessment formats (eg, telephone based) and repeated at 6 months. Cost analysis will be conducted to determine the cost of implementing this intervention. The analysis will include the cost of training the volunteers, taking into consideration the time needed to deliver the group training sessions and the individual competency assessments, and the provision of training materials.

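### The before-after comparison is within-person, but the tests named for skewed and categorical outcomes assume independent samples, and the t-test is not said to be paired

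*Protocol article*

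**What the plan says.** All places are in the Protocol article.

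- **Who is measured.** One group of exercise participants (Exercise participant recruitment): "The aim is to recruit 30 older adults attending social clubs who do not engage in regular exercise". The limitations section concedes that "a limitation of the study is the lack of a control group".
- **When.** Under Secondary outcomes: "These outcome measures will be recorded at baseline, using remote assessment formats (eg, telephone based) and repeated at 6 months".
- **What is compared.** Under Quantitative data analysis: "Outcome measures recorded at baseline will be compared with measurement at 6 months". This covers CHAMPS, Barthel Index, EQ-5D-5L, PRISMA-7 and SARC-F. It is the only inferential comparison described.
- **With which tests.** The same section says: "Depending on the skew of the data, parametric (t-test) or non-parametric (Mann-Whitney U test) statistics will be used for continuous variables". For the rest, a χ² "test will be used for categorical variables". The Abstract repeats the choice: "Parametric(t-test) or non-parametric(Mann-Whitney U test) statistics will be used to analyse continuous variables", again with χ² for categorical variables.
- **What the result is for.** Under Study design, of the measured impact on activity and function: "This will help inform the sample size calculation for a future effectiveness trial".

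Neither the Wilcoxon signed-rank test, nor McNemar's test, nor a t-test described as paired appears anywhere.

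**The concern.** Mann-Whitney U and χ² compare two separate sets of people. Here there is one set of people observed twice, and no second arm or subgroup contrast is described to which a two-sample test could apply. Those tests ignore the correlation between a person's two scores and so use the wrong reference variance.

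The affected branches are likely to be used. The Barthel Index is capped at 100 and SARC-F runs from 0 to 10, so skew is plausible and would send them to Mann-Whitney U. The SARC-F cut-off of 4 and the PRISMA-7 cut-off of 3 give yes/no status, which would go to χ².

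Normality is also to be checked on each outcome measure, whereas a paired analysis needs it for the within-person differences.

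At stake is the ability of a small study to detect a real within-person change, and the quality of what it passes on to the later trial.

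**Working it through.** **Inputs from the article:** 30 participants, one group, two time points, no control group. The article states no effect size, SD, correlation, alpha or power for these comparisons, so there is no planned figure to reproduce.

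**Assumptions:** 30 complete pairs, equal SD of 1 at both times, bivariate-normal scores, two-sided 5% level, within-person correlation r of 0.3, 0.5 or 0.7, and a true change of 0.4 or 0.5 SD.

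**1. Standard error of the mean change.**

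- Treated as independent: √(2/n) = √(2/30) = 0.258.
- Paired: √(2(1−r)/n).
- Ratio: 1/√(1−r).

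| r | SE, independent | SE, paired | Ratio |
|---|---|---|---|
| 0.3 | 0.258 | 0.216 | 1.20 |
| 0.5 | 0.258 | 0.183 | 1.41 |
| 0.7 | 0.258 | 0.141 | 1.83 |

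At r = 0 the two agree and nothing is lost.

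**2. Actual type I error at a nominal 5% (simulated).**

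| r | Mann-Whitney U | χ² |
|---|---|---|
| 0.3 | 2.1% | 2.9% |
| 0.5 | 0.65% | 1.8% |
| 0.7 | 0.05% | 0.7% |

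Every entry is below 5%, so the error is conservative.

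**3. Power of the t-test, true change 0.4 SD (simulated).**

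| r | Unpaired t | Paired t |
|---|---|---|
| 0.3 | 31% | 44% |
| 0.5 | 27% | 56% |
| 0.7 | 23% | 78% |

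Normal-approximation check at r = 0.5:

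- Paired: Φ(0.4/0.183 − 1.96) = Φ(0.23), about 59%.
- Unpaired: Φ((0.4 − 1.96 × 0.258)/0.183) = Φ(−0.58), about 28%.

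Both are close to the simulated values.

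**4. Power of the rank and binary tests, true change 0.5 SD (simulated; binary status cut at +0.5 SD).**

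| r | Mann-Whitney U | Wilcoxon signed-rank | χ² | Exact McNemar |
|---|---|---|---|---|
| 0.3 | 45% | 59% | 31% | 27% |
| 0.5 | 45% | 73% | 29% | 30% |
| 0.7 | 44% | 92% | 26% | 37% |

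The rank-test loss is large. The binary loss is negligible at r = 0.5, and at r = 0.3 exact McNemar has slightly less power than χ².

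**5. A binary illustration.** Suppose SARC-F status of 4 or more falls from 12/30 to 6/30, with six people improving and none worsening.

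- χ² = (12 − 6)²/(30 × 2 × 0.3 × 0.7) = 36/12.6 = 2.86, p = 0.091 (0.159 with continuity correction).
- Exact McNemar: 2 × 0.5⁶ = 0.031.

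This is the most favourable split of the discordant pairs. It shows that the two tests can disagree, not how often they will.

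**The case against.** Several points on the other side stand.

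- **Not every comparison is affected.** A reader might infer that all five instruments will be analysed wrongly. The article does not support that: it says only t-test, and a paired version fits the wording. Outcomes judged near-normal would then be handled correctly. Pairing the t-test with Mann-Whitney U suggests the independent version but does not state it.
- **No false claims of benefit follow.** The error is conservative. A reader might argue that an unpaired test lets all baseline scores be set against 6-month completers only, so that drop-out looks like gain. If 6 of 30 were lost and their baseline lay 0.75 SD below that of completers, the spurious gain would be 0.75 × 6/30 = 0.15 SD. Both figures are assumed, and the article does not say that it will compare those sets.
- **The SD of change is not ruled out.** A reader might infer that it will never be estimated. The Abstract promises descriptive statistics on the intervention's impact, and naming a test does not prevent reporting change scores. A later controlled trial could also be sized from the outcome SD.
- **The simulations use normal data.** Under the article's rule Mann-Whitney U is kept for skewed data, which were not simulated. The rank-test power figures are therefore indicative only.
- **The primary outcomes are untouched.** Recruitment, training, retention, adherence and fidelity concern feasibility, and the tests at issue are applied only to the secondary measures.

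One defence fails: that test selection is a detail left to a fuller plan. The article names Mann-Whitney U and χ² in two places, so a fuller plan with paired tests would have to contradict it.

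**Conclusion.** The concern holds in a limited form, as something that should be fixed. Mann-Whitney U and χ² do not fit a single group measured twice, and the t-test is left ambiguous. The resulting p-values would be invalid in the conservative direction: real change is more likely to be missed, and the false-positive rate falls below its nominal level.

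The size depends on the within-person correlation, which the article does not give. For r between 0.3 and 0.7 the SE of a mean change is overstated 1.2- to 1.8-fold. At r = 0.5, power for a 0.4 SD change is roughly halved. For binary status the practical cost is small at moderate correlation, and the point there is mainly one of validity.

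The feasibility conclusions do not depend on these tests. What could suffer is the reading of the secondary outcomes and, through it, the information handed to the later trial.

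**What to change.** In the Abstract (Analysis) and in Quantitative data analysis:

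1. State that the t-test is paired, and assess normality on the within-person differences.
2. Replace Mann-Whitney U with the Wilcoxon signed-rank test on within-person change.
3. Replace χ² with exact McNemar for binary status, or a marginal homogeneity test where there are more than two categories.
4. State that these comparisons use participants with both measurements.
5. Report the change in continuous outcomes with its SD and a 95% CI, since the article intends the measured impact to inform a later sample size.

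The cost is a few sentences of wording. It needs no new data, visits or participants, and the tests are available in the SPSS package already named.
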